### Statistical analyses

Main effects of stress exposure (stress vs control group) on alcohol consumption (amount of alcoholic beverage consumed) will be determined using linear regressions adjusting for the amount of non-alcoholic beverages consumed (which reduces unspecific variance in outcome). However, in case of considerable by chance differences in baseline characteristics between the two groups despite randomization, these characteristics will be included in the regression model if they are associated with alcohol consumption. To address potential biases related to missing data, we will conduct sensitivity analyses using multiple imputation.

Moderation analyses: Moderators are defined causally [50]. Linear regressions with interaction terms will be applied to test whether stress effects on alcohol consumption are moderated by childhood maltreatment, hair cortisol concentration and trait impulsivity (with main effects terms and interaction term, e.g. group × childhood maltreatment). Significant interactions indicate that a respective factor (moderator) predicts different effects of stress on alcohol assumptions. To approach causal conclusions, we will fit these models again while adjusting for shared factors of moderators and outcomes (e.g. previous stressful events, previous alcohol use) [50].

Mediation analyses: Mediators are also defined causally according to the counterfactual definition of Robins and Greenland [115] that is implemented in the ‘paramed’ package in Stata. This module allows dividing the estimated total stress effect (stress vs. control group) on alcohol consumption into a direct effect and an indirect effect mediated through stress reactivity (saliva cortisol, alpha amylase, self-reported stress), impulsivity (delay discounting), inhibitory control, and motivational sensitization (attentional bias). Mediation analyses will be adjusted for putative sociodemographic (e.g. age) and other shared factors of a potential mediator and outcome (e.g. time of day, preference of beer) as well as for the mentioned factors for moderation. The alpha level will be specified at two-sided 0.05. If necessary, the analyses will be repeated with robust standard errors (via the sandwich estimator) and robust linear regressions [116]].

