## Methods/design

### Study design

The MESA study is a randomized controlled study that started in December 2018 and is being conducted in a laboratory setting at the Medical School Hamburg. The study is divided into an online screening and a main examination, with detailed description in the following (“Procedure” section). The study has a four-group design. Participants are stratified into equal groups of regular and risky drinkers (with regular drinking being defined as average daily alcohol consumption of less than 24 g over the past 30 days and risky drinking being defined as average daily alcohol consumption of more than 24 g over the past 30 days [51]). Regular and risky drinkers are then randomly assigned to either an experimental (acute stress) or a control condition (Fig. 1).

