### Recruitment and screening procedures

Participants are recruited via personal contacts, flyers and advertisement in university and public settings in Hamburg (cafés, bars, supermarkets, sports clubs; student dormitories) as well as via social media (e.g. Instagram, Facebook) and student job markets. In addition, advertising is made in lectures and on the university website.

All individuals willing to participate in the study have to complete an online screening in advance of the main assessment, where basic demographic variables as well as all in- and exclusion criteria are assessed. Further, the usual alcohol consumption is measured using a self-administered timeline follow-back consisting of a calendar on which participants provide retrospective reports of average daily alcohol intake for the past 30 days [58]. The information on daily alcohol consumption is used to allocate participants to the groups of regular and risky drinkers. All individuals meeting the inclusion criteria are then invited to participate in the main study.

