### Ad-libitum taste test

After completion of the behavioral tasks and the intervention, participants are asked to take part at an ad-libitum taste test as a covert measure for alcohol consumption. The ad-libitum taste test is a widely used method, which provides an unobtrusive and indirect measure of participants’ motivation to drink alcohol [84]. All participants are given two 0.33 l glasses of beer (two brands each containing 5% alcohol) and two 0.33 l glasses containing different soft drinks. Participants are instructed that they have 15 min to taste each glass to rate qualities about each drink (e.g. gassy, bitter). Participants are told to drink whatever amount necessary to make accurate judgements. The dependent variable is the amount of alcoholic beverage (beer) consumed and can range between 0 and 666 ml (equals 26.64 g ethanol). Non-alcoholic drinks are presented to control for the potential effect of thirst. The ad-libitum taste test is a valid method for the assessment of alcohol intake in the laboratory supported by strong associations between ad-libitum consumption and typical alcohol consumption [84]. It is also robust against several potential confounders such as time of day or participant awareness [84]. The taste test has been used to investigate a number of potential influences on alcohol consumption, including alcohol cues [102, 103, 104], impulse control [105, 106], and social influences [107], and it has been used to establish initial proof of concept for novel behavioral interventions [108, 109, 110].

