### Study progress and preliminary feasibility data

The data collection of the presented MESA study started in December 2018. From December 2018 until March 2022 N = 623 persons participated in the online screening. A total of 213 complete data sets have been collected so far. All participants are male and between 18–40 (*M* = 25) years old. 97 of the 213 participants took part in the stress condition, stratified in 40 risky drinkers and 57 regular drinkers. Further, 117 participants took part in the control condition stratified in 36 risky drinkers and 81 regular drinkers. More than half reported they were university students.

Due to the Covid-19 pandemic, the study was paused in the beginning of March 2020 in order to protect the safety and health of all personnel involved in the study and to comply with legislative regulations. The laboratories reopened in September 2021 and data collection was continued.

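### The H1 model admits baseline covariates only on observed imbalance and outcome association, without thresholds, so drinking stratum and usual intake are not guaranteed to be in it

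*Protocol article*

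**What the plan says.** **Main-effect model.** The Statistical analyses section of the protocol article sets out "linear regressions adjusting for the amount of non-alcoholic beverages consumed" for the effect of condition on beer consumed. That is the only covariate that always enters.

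**Rule for baseline characteristics.** They are considered "in case of considerable by chance differences in baseline characteristics between the two groups despite randomization", and then "these characteristics will be included in the regression model if they are associated with alcohol consumption". Both conditions must hold. The section does not say what size of difference counts, how association is judged, or which characteristics are candidates.

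**Stratification.** Under Study design: "Participants are stratified into equal groups of regular and risky drinkers". The strata come from the screening timeline follow-back: "The information on daily alcohol consumption is used to allocate participants to the groups of regular and risky drinkers" (Recruitment and screening procedures).

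**Prognostic value of usual intake.** The Ad-libitum taste test section supports the validity of the outcome by "strong associations between ad-libitum consumption and typical alcohol consumption". Person-related measures also lists usual consumption among the variables that might affect the associations of interest.

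**Where earlier drinking is named.** The refitted moderation models involve "adjusting for shared factors of moderators and outcomes (e.g. previous stressful events, previous alcohol use"), and the mediation models take over the same factors. The main-effect model names neither earlier drinking nor stratum.

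**The concern.** Under this rule the baseline part of the H1 model is settled only after the trial data have been seen, and the second condition uses the outcome itself. Since neither condition has a threshold, two careful analysts could fit different primary models to the same data.

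The rule also relies on the wrong criterion. Adjustment in a randomised comparison is worthwhile because a covariate predicts the outcome, whether or not the arms happen to differ on it. The section uses that very argument for soft-drink volume, which it includes to reduce unspecific variance, but does not apply it to usual intake.

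Stratified randomisation makes this worse for the stratum. Its purpose is to balance that factor, so the more successful it is, the less likely the imbalance condition is to admit the factor. At stake are the precision of the H1 estimate, its bias conditional on whatever imbalance occurs, and the reader's confidence that the model was not chosen with the result in view.

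**Working it through.** **Inputs.** From the article: two-sided alpha 0.05; 200 per stratum and 100 per cell, 400 in all; stated power 0.80 to 0.95; interim counts of "97 of the 213 participants took part in the stress condition, stratified in 40 risky drinkers and 57 regular drinkers", and 36 risky and 81 regular of 117 in control. Assumed, because no figure is given: share of outcome variance explained by stratum and usual intake, R² = 0.10 to 0.20; difference in beer consumed between strata, 0.5 to 1.0 SD.

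**1. The plan's power figure.** No effect size or SD is stated, so 0.80 to 0.95 cannot be reproduced, only back-solved (normal approximation, equal arms of n): d = (1.960 + z_power) / √(n/2).
- Within one stratum, n = 100 per arm: 2.802/7.071 = 0.396 for 0.80; 3.605/7.071 = 0.510 for 0.95.
- Pooled, n = 200 per arm: 2.802/10 = 0.280 for 0.80; 3.605/10 = 0.360 for 0.95.

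**2. Gain from prespecified adjustment.** The residual SD becomes √(1 − R²), so power = Φ(d√(n/2)/√(1 − R²) − 1.960). Starting from 0.80:
- R² = 0.10: 2.80/0.949 = 2.95; Φ(0.99) = 0.839.
- R² = 0.20: 2.80/0.894 = 3.13; Φ(1.17) = 0.879.

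The results are the same for d = 0.396 with 100 per arm and d = 0.280 with 200 per arm. In the pooled case the number needed for 0.80 falls from 201 per arm to 181 and 161.

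**3. What the rule recovers.** A simulation used 100 per arm, five baseline covariates of which one was prognostic, balance left to chance, and 2,500 runs per setting. Imbalance and association were each judged at p < 0.05.

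| R² | Unadjusted power | Power under the rule | Power, prespecified |
|---|---|---|---|
| 0.10 | 0.804 | 0.811 | 0.847 |
| 0.20 | 0.793 | 0.801 | 0.875 |

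The prognostic covariate entered in about 5% of runs. With imbalance read as a standardised difference above 0.2, it entered in about 15% to 17%; power at R² = 0.20 was then 0.816, 0.832 and 0.886. Type I error under the rule lay between 0.038 and 0.052 across all settings.

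**4. Interim stratum balance.**
- Risky share: 40/97 = 41.2% under stress, 36/117 = 30.8% in control; difference 0.105.
- Fisher exact p = 0.117.
- Standardised difference: 0.1047/√[(0.412 × 0.588 + 0.308 × 0.692)/2] = 0.1047/0.477 = 0.22.

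A p < 0.05 criterion leaves stratum out. A criterion of more than 0.2 meets the first condition, and stratum then enters if it is associated with the outcome.

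**5. Shift in a pooled estimate that omits stratum.** Shift = 0.1047 × difference between strata: 0.1047 × 0.5 = 0.05 SD and 0.1047 × 1.0 = 0.10 SD, in the hypothesised direction.

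The arm counts sum to 97 + 117 = 214, not the stated 213. One participant either way does not change these conclusions.

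**The case against.** The strongest defence has four parts.

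- **The rule is written in advance and does no measurable harm to the test.** This stands. A reader might infer inflated type I error from data-driven selection, but the simulation found none when the rule is applied mechanically. What it cannot cover is choice among readings of an undefined threshold.
- **Omitting the stratum does not make the test invalid.** This stands. A reader might take an analysis that ignores the stratification factor to have standard errors that are too small. With a prognostic factor balanced by design they are typically too large, so the error is conservative and costs power.
- **The imbalance is interim, and the rule might catch it.** This stands in part. Only about half of the 400 had been studied; if 100 per cell is reached, strata are balanced and the shift is zero. The text never mentions significance, so it does not show that the stratum would be left out. That the answer turns on an unstated criterion is the point.
- **The stratum may be handled elsewhere.** Power is given per stratum, and several hypotheses separate or compare the strata. If H1 is fitted within strata, stratum imbalance cannot bias it. The Statistical analyses section does not say so, and continuous intake would still be unadjusted within each stratum.

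A full analysis plan, not shown, could supply thresholds and covariate lists. It could not make both variables certain to enter without replacing the stated rule.

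**Conclusion.** The point holds for the H1 main-effect model. The stated rule gives no assurance that either the stratification factor or the article's own named correlate of taste-test consumption will be included, and it leaves the choice of baseline covariates to be settled on seen data.

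The loss is mainly one of precision: power of 0.80 where about 0.84 to 0.88 was available, if stratum and usual intake explain 10% to 20% of outcome variance beyond what is already in the model. In simulation at R² = 0.20 the rule recovered 0.008 of a possible 0.082. Conditional bias of about 0.05 to 0.10 SD applies only to a pooled model without stratum, at the interim imbalance and the assumed difference between strata.

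A reader might set that shift against target effects of 0.40 to 0.51. Those back-solved values belong to within-stratum tests, where the shift cannot arise; the pooled counterparts are about 0.28 to 0.36, and the article states neither. Nor is the whole model conditional: soft-drink volume always enters. The change should be made, but nothing here invalidates the trial.

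**What to change.** Replace the imbalance-and-association rule with a fixed covariate set, for example: *The main-effect model will include drinking stratum and continuous timeline-followback intake at screening, irrespective of observed balance between conditions.* Report a model with condition and stratum only as a sensitivity analysis.

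State whether H1 is tested in the pooled sample or separately within strata. If within strata, say so and still adjust for continuous intake.

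The cost is a sentence or two in the analysis plan. Both variables come from the screening timeline follow-back that every participant completes, so no new data are needed. The change should be recorded before outcomes are compared between conditions.

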
Regarding the underlying mechanisms of the relationship between stress and alcohol consumption, the idea of alcohol use as a dysfunctional coping strategy to self-medicate aversive emotional states following stressful experiences has long been the predominant model [32]. Although there is considerable empirical support for the self-medication hypothesis [32, 33, 34, 35], it is not able to fully explain the association between stressful experiences and alcohol use. Alcohol consumption does not necessarily reduce aversive emotional states [36, 37], violating the negative reinforcement assumption underlying the self-medication hypothesis. Therefore, knowledge on additional mechanisms beyond self-medication at different stages of alcohol use progression is required to explain the association between stress and alcohol use. Several relevant psychological and biological factors that might affect this relationship have been described in the literature [20, 38]. Acute stress activates an immediate reaction increasing cerebral and peripheral adrenalin and noradrenalin and a delayed endocrine response (via HPA axis) increasing glucocorticoids (mainly cortisol in humans) [39]. These systems affect different mechanisms relevant to alcohol use depending on the stage of alcohol use progression. At early stages of alcohol use progression, alcohol use leads to increased autonomic arousal and HPA axis activation. These effects potentiate both stress and alcohol-related effects on motivation and reinforcement learning [40] which can further facilitate alcohol use as a stress-related coping mechanism [38]. It further promotes the salience of drug-related cues known as attentional bias as these cues ‘grab the attention’ and further increase alcohol craving [41]. At later stages of alcohol use progression, binge and excessive alcohol consumption results in larger-scale adaptations in terms of a neuroendocrine tolerance response to stress and alcohol intake [10, 42] which may be involved in the transition from controlled to compulsive alcohol consumption [10, 43]. Also, a sensitization of motivational systems can manifest, again, in priority processing alcohol-related cues, i.e. attentional bias [44, 45]. The stress-induced sensitization at later stages of alcohol use progression is assumed to be active in parallel to the noradrenalin-related mechanisms [18]. Taken together, stress and stress system alterations by alcohol consumption could be associated with biased information processing, increased impulsivity and impaired control functions; a pattern that is known to be a key mechanism in the development of excessive alcohol use [46, 47].

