### Aims and hypotheses

The present and ongoing study aims to fill this research gap by conducting an experimental laboratory design to investigate the underlying mechanisms of the association between stress and alcohol consumption (MESA) in the at-risk population of young men. Since these mechanisms are expected to differ depending on the stage of alcohol use, they are examined in regular and risky drinkers. Therefore, several processes that could mediate the relation between stress and alcohol consumption at different stages of alcohol use progression are assessed.

The research questions are as follows:Does acute stress increase alcohol consumption in a laboratory setting?What are the mediators of the association between acute stress and alcohol use?What are the moderators of the association between acute stress and alcohol use?Are effects of acute stress on alcohol use as well as moderators and mediators of this association different in risky drinkers compared to regular drinkers?

The following a priori hypothesis were formulated:Acute stress increases alcohol consumption in a laboratory setting.This effect is stronger in risky compared to regular drinkers.Emotional distress, endocrine and autonomic stress reactivity as well as impulsivity account for most of the effect of stress on alcohol use in regular drinkers (mediation).Emotional distress, endocrine and autonomic stress reactivity, impulsivity, attentional bias and craving account for most of the effect of stress on alcohol use in risky drinkers (mediation).A history of childhood maltreatment, basal HPA-axis activity and impulsivity are related to a stronger effect of acute stress on alcohol consumption in regular and risky drinkers (moderation).

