### Sample storage, biochemical analyses and data preparation

The saliva samples are taken using salivette ‘code blue’ devices (Sarstedt, Nümbrecht, Germany) directly before the intervention and at three time points after the intervention (Fig. 5). Saliva samples are stored at − 20 °C in a laboratory freezer. After thawing, saliva samples will be centrifuged for 10 min at 4000 rpm. Salivary cortisol concentrations will be determined using a commercially available chemiluminescence assay (CLIA, IBL-Hamburg, Germany). Concentrations of salivary alpha-amylase will be detected by using an in-house enzyme kinetic method according to the protocol described in [63]. Hair cortisol concentrations will be determined via liquid chromatography tandem mass spectrometry (for detailed information on analysis methods see [56]).

Dimensional variables that are not normally distributed (expected e.g. for hair cortisol concentration, salivary cortisol and alpha amylase) will be Box–Cox transformed towards normal distribution. For all biological and behavioral variables, participants with outlying values of more than three standard deviations above the mean will be excluded from the respective analysis. Besides, robust linear regressions will complement conventional linear regressions because they down weight observations with large residuals to meet the assumption of equal variances of residuals. Composite measures of the entire cortisol secretion during the TSST (area under the curve with respect to ground; AUC_G_) and the cortisol stress reactivity (area under the curve with respect to increase; AUC_i_) will be calculated [112]. Analysis with these variables will be adjusted for initial cortisol concentration to alleviate confounding risk as AUC variables may be comprised of variance due to stress reactivity and stress-unrelated HPA axis activity [113]. All analysis including cortisol secretion during the TSST will be run twice with all participants in the first and with exclusion of non-responders to the TSST (increase of 1.5 nmol/l compared to baseline [114]) in the second run. With regard to alpha-amylase, both AUC measures and peak minus baseline levels will be calculated.

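### The third and fourth hypotheses are about a set of mediators, but the mediation analysis defines no joint indirect effect and its mediator list matches neither set

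*Protocol article*

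**What the plan says.** **Hypotheses.** In Aims and hypotheses, the third hypothesis (H3) says that emotional distress, endocrine and autonomic reactivity and impulsivity "account for most of the effect of stress on alcohol use in regular drinkers (mediation"). The fourth (H4) is for risky drinkers: "Emotional distress, endocrine and autonomic stress reactivity, impulsivity, attentional bias and craving account for most of the effect". Both are claims about a set, within one drinking stratum.

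**Analysis.** Statistical analyses adopts a counterfactual definition of mediation and divides the total stress effect "into a direct effect and an indirect effect mediated through stress reactivity" (salivary cortisol, alpha-amylase, self-reported stress), then continues the list with "impulsivity (delay discounting), inhibitory control, and motivational sensitization (attentional bias"). Adjustment is for sociodemographic variables and "other shared factors of a potential mediator and outcome (e.g. time of day, preference of beer"), plus the factors used for moderation. The paragraph gives no joint indirect effect and no meaning for *most*.

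**Links between mediators.** The background section Mediators and moderators says that the stress systems act on other mechanisms relevant to drinking, that early-stage activation promotes attentional bias and so craving, and, more cautiously, that "stress and stress system alterations by alcohol consumption could be associated with biased information processing, increased impulsivity and impaired control functions".

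**Cortisol.** Sample storage, biochemical analyses and data preparation defines two cortisol composites, AUC_G and AUC_I, and adds: "Analysis with these variables will be adjusted for initial cortisol concentration".

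**The concern.** The planned quantity and the hypotheses do not meet. A direct and indirect effect for one mediator answers how much runs through that mediator. H3 and H4 ask how much runs through several together. Where mediators are linked, the first kind of answer cannot be assembled into the second: adding single effects counts shared routes twice, and reading them one by one can miss a joint majority.

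There is also an identification problem. If stress raises cortisol, and cortisol affects both impulsivity and drinking, then cortisol is a confounder of the impulsivity–drinking relation that is itself changed by stress. The natural indirect effect through impulsivity is then not identified by adjusting for baseline factors, and the adjustment examples given (age, time of day, beer preference, earlier stress, earlier alcohol use) are of that kind.

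At stake is whether the trial can say that H3 or H4 was supported or refuted.

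**Working it through.** **1. Figures in the plan.** The article gives no figure for mediation. Its only power statement (0.80 to 0.95 at 200 per stratum) concerns ANOVA F tests and does not bear on this point. All path coefficients below, and the reading of *most* as above 50%, are assumptions.

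**2. Hypothesised sets against the analysed list.**

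| Process | H3 | H4 | Table 1 | Statistical analyses |
|---|---|---|---|---|
| Impulsivity (delay discounting) | yes | yes | mediator | yes |
| Endocrine and autonomic reactivity | yes | yes | mediator | yes |
| Attentional bias | no | yes | mediator | yes, not limited to risky drinkers |
| Craving | no | yes | confounding variable | absent |
| Inhibitory control | not named | not named | mediator | yes |

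Even if the list is read as one joint indirect effect, it is the effect of a different set from H3 or H4.

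**3. Two-mediator example (SD units).** Stress→cortisol 0.8; cortisol→impulsivity 0.4; stress→impulsivity 0.1; cortisol→drinking 0.2; impulsivity→drinking 0.3; direct 0.3.

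- Stress effect on impulsivity: 0.1 + 0.8 × 0.4 = 0.42.
- Joint indirect: 0.8 × 0.2 + 0.42 × 0.3 = 0.286. Total: 0.586. Joint share: 0.286/0.586 = **49%**.
- Cortisol alone: 0.8 × (0.2 + 0.4 × 0.3) = 0.256, or 44%.
- Impulsivity alone, cortisol left out: its coefficient becomes 0.3 + 0.2 × 0.4 = 0.38, giving 0.42 × 0.38 = 0.160, or 27%.
- Sum: 0.416/0.586 = **71%**.

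The excess of 0.130 has two parts. The route stress→cortisol→impulsivity→drinking is counted twice (0.8 × 0.4 × 0.3 = 0.096), and cortisol confounds the impulsivity coefficient (0.42 × 0.08 = 0.034). The 0.38 assumes a within-group SD of 1 for impulsivity. If its own residual SD is 1, the coefficient is 0.3 + 0.08/1.16 = 0.369 and the sum is 70%. The part of impulsivity's effect that is independent of cortisol is only 0.1 × 0.3/0.586 = 5%, against the 27% that a single run would show.

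**4. Varying the link d from the first to the second mediator.** Stress paths 0.6 each, drinking paths 0.2 each, unit residual SD; the direct effect is set to give the stated joint share. Formulas: S1 = a1(b1 + d·b2); S2 = (a2 + a1·d)(b2 + b1·d/(1 + d²)).

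| True joint share | d | First alone | Second alone | Sum |
|---|---|---|---|---|
| 40% | 0 | 20% | 20% | 40% |
| 40% | 0.3 | 23% | 29% | 51% |
| 40% | 0.5 | 24% | 34% | 58% |
| 60% | 0 | 30% | 30% | 60% |
| 60% | 0.3 | 34% | 43% | 77% |

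With unlinked mediators the sum is exact. Reading shares singly can miss a joint majority even then (30% and 30% against 60%).

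**5. Five mediators at n = 200, 2000 simulated runs.** Stress paths 0.5, drinking paths 0.12, the first mediator acting on the others with d = 0.3.

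- True joint share 40%: the sum exceeds 50% in 82% of runs and the joint estimate in 19%. The two verdicts differ in 64% of runs, against about 7% at d = 0.
- True joint share 60%: the joint estimate exceeds 50% in 70% of runs; any single share does so in 6%.

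**6. Secondary: AUC_G and AUC_I.** With equal sampling times, AUC_I = AUC_G − T × initial cortisol, where T is the sampling duration. Then β·AUC_G + γ·C0 = β·AUC_I + (γ + βT)·C0. Once initial cortisol C0 is in the model, the coefficient, standard error, p-value and group effect on the mediator are the same for both composites. This needs the same participants and untransformed composites.

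**The case against.** **One-at-a-time analysis is an inference.** The sentence has one indirect effect followed by a list, and says neither separately nor jointly. The singular wording on confounders leans towards separate runs but does not settle it. This stands, and nothing here relies on what the named software can do. It does not rescue the plan, because the list read jointly still matches neither set.

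**The links are partly tentative.** The sentence on impulsivity and control functions speaks of possible association and concerns alterations by alcohol consumption, and the same section describes some mechanisms as acting in parallel. A reader might infer that the mediators are known to cause one another within the session. The article does not establish that; its firmer statement concerns attentional bias and craving.

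**No rule in the plan adds single shares.** In the example of step 3 both single shares are below 50%, so reading them singly agrees with the true 49%; only summing reverses it. This stands: reversal needs a particular reading rule, and the article states none.

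**An article may leave such detail to a fuller document.** That covers the threshold and model specification. It does not cover a stated analysis whose mediator list conflicts with the stated hypotheses.

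**The AUC identity is fragile.** Box–Cox transformation and the 3 SD exclusion are planned. In a simulation with assumed log-normal cortisol (n = 200, 500 runs), Box–Cox applied to the composites and baseline gave a median p-value difference of 0.18, with significance differing in 11% of runs. The exclusion alone gave 0.09 and 8%. If Box–Cox is applied to the raw samples before the AUCs are formed and nobody is excluded, the identity survives. The article does not fix the order, nor does it present the two composites as separate mediators.

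**Conclusion.** The concern holds in this form: H3 and H4 are claims about sets within strata, the analysis as written defines no joint indirect effect for them, and its list matches neither set. That follows from the text alone and is worth correcting.

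The size of the possible error is conditional. Under the assumed paths, summing turns a true 40% to 49% into 51% to 71% with two mediators, and single reading misses a true 60%. A reader might conclude that the trial's verdict will be reversed. The documents do not support that: for a false majority by summing, the mediators must be linked, the true share must lie near the threshold and someone must add the shares; a missed majority needs shares to be read singly.

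The identification problem is likewise conditional on a stress-induced mediator affecting a later one and drinking. Agreement between AUC_G and AUC_I should not be taken as corroboration, but a reader should not infer that they always give identical results.

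**What to change.** - In each drinking stratum, test H3 or H4 by the joint indirect effect of exactly the hypothesised set. Fit an outcome model with stress, all mediators of the set and baseline covariates; take joint share = (total − direct)/total, with a bootstrap interval. This form assumes no stress-by-mediator interaction. Report the total and direct effects beside the share, because the ratio is unstable when the total effect is small.
- Define *most* as a joint share above 50%, and say in advance whether the estimate or the lower limit must exceed it.
- Align the lists. Treat craving as a mediator for H4 and not as a confounder, provided that it is measured after the intervention; the text does not say when. Either name inhibitory control in the hypotheses or label it as additional.
- Report single-mediator results as descriptive and not additive. Effects ordered along a sequence of mediators should not be requested, since the protocol states no order, and cortisol sampling up to 24 minutes after induction may overlap with the tasks.
- State that agreement between AUC_G and AUC_I, both adjusted for initial cortisol, is not independent support.

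Cost: plan wording and different code on the same data, subject to the timing of the craving measure. The downside is wider intervals: in step 5, with a true joint share of 60%, the joint estimate passed 50% in only 70% of runs at n = 200.
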